**Nature and extent of the burden and risks associated with participation, benefit and group relatedness:**

Participation in the care pathway is non-invasive. It includes specialized care for older adult patients presenting with NSCs at the emergency department. The burden regarding participation in this care pathway can be considered minimal

## **2. INTRODUCTION AND RATIONALE**

Older adults, often frail, frequently present with poorly-defined symptoms leading to an extensive differential diagnosis [1]. These so called ‘non-specific’ complaints (NSCs), such as: ‘feeling unwell’, ‘feeling fatigued’ or ‘feeling dizzy’, are expressions of an acute medical problem in 50% of the cases [2]. Health care providers are challenged in the care of older adults with NSCs, due to their comorbidities, deteriorating cognition and the subjective nature of their complaints [3]. Therefore, a care pathway delivering special care for the older adult with NSC and concurrently providing an overview of the health status of a patient, might add value. Data from this care pathway can be used to guide a management protocol for elderly patients with NSCs at the emergency department (ED) to improve the quality of care.

Studies have shown that patients with NSCs have different characteristics compared to patients with specific complaints (SCs) [4]. Patients with NSCs have more comorbidities, use more medications, are at a higher risk of functional decline due to longer hospitalization and have a higher 30-day mortality rate compared to patients with SCs. Undertriage and unnecessary testing often contribute to a prolonged ED stay and frequent readmissions [5]. Furthermore, clinical experience of the health care provider seeing the patient with NSCs impacts diagnostic accuracy [6]. We aim to implement an integrated care pathway in different emergency departments of the Brabant area, focused on streamlining the care of patients with NSCs at the ED. This will be accomplished by evaluating the NSC in-depth (primary care), performing APOP (triage at the ED), screening certain domains of the CGA if a patient is high-risk according to APOP (somatic, nutrition, psychosocial, functional, mobility, falls), performing a standard set of diagnostic tests (at least: ECG, lab, urinalysis, X-thorax and bladder scan) and providing ‘specialized care’, as described in the methods section. In this care pathway, we will guide actions according to the APOP-risk score. After admission, a verification and review of the medication list will be performed. We hypothesize that the care pathway will primarily improve patient satisfaction and reduce the ED-length of stay. Reduced hospital length of stay, decreased 30-day mortality, improved functional status (daily activities, mobility, cognition), a reduction of (re-)admission rates for older adults with NSCs and reduced costs of care for this patient population might follow as a result of implementing this care pathway.

## **3. OBJECTIVES**

1. The **primary objectives** of the care pathway are to evaluate:

- Length of stay at the ED (ED-LOS)
- Patient satisfaction on 4 domains

1. relief of symptoms (degree of relief and symptoms, duration until symptom relief, impact on function)
2. understanding the diagnosis and cause of symptoms, understanding prognosis
3. presence and understanding of the diagnostic, therapeutic and follow-up plan
4. reassurance during ED-stay

2. The **secondary objectives** of the care pathway are to evaluate:

- Length of stay at the hospital (HOSP-LOS)
- Discharge destination
- Medical diagnosis (at admission versus discharge)
- Frequency of readmissions / revisits
- 30-day mortality
- Loss of functional status
- Costs-effectiveness of the care pathway

## **4. METHODS**

### **STUDY DESIGN**

The following organizations will implement the care pathway:

- Catharina Ziekenhuis, Eindhoven, the Netherlands
- ETZ (Elisabeth-TweeSteden Ziekenhuis), Tilburg, the Netherlands
- Jeroen Bosch Ziekenhuis, 's Hertogenbosch, the Netherlands
- Maxima Medisch Centrum, Veldhoven, the Netherlands
- St. Anna ziekenhuis, Geldrop, the Netherlands
- General practitioners of the Brabant area
- Nursing homes

Optional hospitals:

- Amphia, Breda, the Netherlands

Inclusion will take place during approximately 6 months after initiation of the study on workdays between Monday – Friday from 11:00 am – 20:00 pm.

The first hospitals were planned to initiate the study and start implementation of the care pathway and data collection in December 2019 or at the earliest possibility after approval of the study protocol. Due to the COVID-pandemic and its burden on hospital-care throughout the Netherlands, implementation could not take place as planned. The Jeroen Bosch Hospital had started the care-pathway, but had to discontinue after a few weeks due to the massive burden of COVID-care.

Considering that the COVID-pandemic, which resulted in a drop of regular care, may have had an influence on the processes in the ED and the number of elderly people presenting with non-specific complaints, it was decided to temporarily withhold the inclusion of control patients and implementation of the care-pathway. The estimation was made that the COVID-pandemic would be a great confounder in results when comparing a pre-pandemic and post-pandemic population. Therefore it was decided to start over with inclusion of the control-group. In July and August 2020 the participating hospitals were consulted and asked if they had resumed their usual care and how their ED and population had changed. All hospitals agreed to restart inclusion of the control-group from August 2020 onward. Since the numbers of elderly people with non-specific complaints are

expected to be lower than before the COVID-pandemic, it is possible that the period for inclusion for the control group has to be extended. The planned start for implementation of the care-pathway is January 2021, dependent on inclusion of the control-group and the evolution of the COVID-pandemic.

At this moment, October 2020, we are experiencing a second wave of the COVID-pandemic throughout the Netherlands. During the first outbreak, the hospitals in Noord-Brabant especially were in state of crisis, with a drop in the rates of regular care. With this impact in mind, we decided to withhold the care-pathway and include a post-COVID control-group. However, the global opinion is becoming that COVID is here to stay, and it will become part of the day to day business both at social and hospital-level. Therefore the aim of hospitals throughout the Netherlands is to arrange the COVID care in the best possible manner, but also assuring regular care to continue as much as possible. With this in mind, the research team decided not to further postpone the inclusion of the control group and planned implementation of the care-pathway is estimated at January 2021. We are aware of the changes in organisation of care that come with the periodical higher burden of COVID-care, so we plan to monitor changes in organisation at the Emergency Department during the inclusion period in each participating hospital.

## 5. STUDY POPULATION

### 5.1.1 Population

Older adult patients presenting with a non-specific main complaint at the practice of their general practitioner (GP) will be screened for inclusion. If a patient meets the inclusion criteria, the GP will refer the patient to a hospital that implemented the care pathway and notify the specialist at the ED (internist, ED-doctor or elderly care physician). Every referring care professional will have a card, which provides information on how to refer a patient to the care pathway and to whom. Patients not referred by the GP can enter the care pathway in several other ways:

- if referred by the practitioner at a nursing home
- if triage at the ED points to a NSC

### 5.1.2 Inclusion criteria

In order to be eligible to participate in this study, a subject must meet all of the following criteria:

- Indicated for admission to hospital, **and**
- Age  $\geq$  70 years, **and**
- A non-specific main complaint at presentation, such as:—
  1. somatic problems:
    - *weakness*: physical weakness in the body limiting the patient to perform daily activities
    - *not feeling well*: patients expressing a passive behaviour due to not feeling well physically or mentally
    - *change in nutritional status*: an abrupt decline of eating and/or drinking, compared to previous eating habits
    - *unexplained weight loss*: an ongoing weight loss or recent weight loss of more than 10% of baseline in the previous month, not related to a modified diet or exercise
  2. a higher demand of care:

- *loss of independency*: an abrupt or ongoing decline of being able to perform daily activities independently
- *a necessity for a change in the living situation*, due to a higher demand of care
- *a necessity for 24-7 care*, not indicated previously

3. cognitive problems:

- *disorientation*: inability to recall current date, name or current environment
- *changes in behaviour*: unexplained agitation, abrupt changes in behaviour
  - *cognitive decline*: abrupt decline in cognitive performances

4. functional status:

- *loss of mobility*: change in functional status leading to limited mobility

5. unexplained falls: a fall not related to extrinsic factors such as poor lighting, unsafe stairways, and irregular floor surfaces or to a precise medical or drug-induced cause

### **5.1.3 Exclusion criteria**

A potential subject who meets any of the following criteria will be excluded from participation in this study:

- Specific (main) complaint coupled to a diagnosis (pain, dyspnea, cough, localised weakness, swollen extremity, diarrhea, dysuria, bleeding, syncope, skin lesions, vertigo, palpitations, e.g.)
- Age <70 years
- Patient refusing data collection or participation in the care pathway

### **5.1.4 Control group**

For patients included in the study as controls, the same inclusion and exclusion criteria apply.

Controls will not be specifically asked for informed consent, as each participating hospital will sign a form to collect data for control patients prior to implementing the care pathway. Additionally, it is the responsibility of each participating institution to inform their patients on the policies regarding data collection in study settings.

Obtaining the retrospective control-group will be done by CTcue, if possible. CTcue is a search engine in which unstructured data from an Electronic Health Record (EHR) can be easily found by adding specific queries in to the search engine. These data will be retrieved anonymously according to our defined in- and exclusion criteria, study parameters and endpoints. Specialists at the ED will be unaware of the patients functioning as controls during this study, since data for controls will be collected retrospectively. After 30 and 90 days, the research nurse will evaluate complications that occurred after the patient leaves the care pathway.

In the participating hospitals without access to CTcue, control patients will be gathered prospectively. The ED specialist will save the patient-number of eligible patients in the care pathway (before it is implemented). The specialist in charge of the patient is allowed to use patient data for research, without consent when data is anonymised. The specialist may grant this right to a third party, in this case the research team. This exchange of data has to be approved by the involved departments, which will be the department of Internal Medicine, Geriatrics and the Emergency Department.

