**Intervention:** If feasible, an ED-coach (passive or active form) will be appointed to each participant of the care pathway. The NSC will be evaluated in-depth, the patient will undergo APOP-screening during triage and if indicated, a comprehensive geriatric assessment will be performed after discharge from the ED at another department. The patient will be seen by a specialist or experienced resident in training at the ED, who will order a standard set of diagnostic tests and review the results. The APOP-risk score will guide further actions in the care pathway. A verification of the medication list will be performed <24 hours and a review of the medication will follow during admission.

**Control cohort:** Recruitment of controls will occur before implementation of the care pathway and on workdays between Monday – Friday from 11:00 am – 20:00 pm. The study period is estimated at approximately 6 months, according to study protocol. Each participating hospital will inform participants regarding their policy on data collection prior to implementing the care pathway. Data for controls within hospitals with access to CTcue will be collected retrospectively. The other participating hospitals will include eligible patients prospectively for the same estimated study period. After 30 days, the research nurse will evaluate complications that occurred after the patient leaves the care pathway.

**Main study parameters/endpoints:** Main endpoints are to evaluate the length of stay at the ED (ED-LOS) and exploring patient satisfaction on 4 established domains. Secondary objectives are evaluating the length of stay at the hospital (HOSP-LOS), discharge destination, medical diagnosis (at admission versus discharge), frequency of readmissions / revisits, 30-day mortality, loss of functional

status and costs-effectiveness of the care pathway. Study parameters are age, gender, main non-specific complaint, main diagnosis at ED-arrival and discharge, way of arrival (per ambulance, public transportation, etc.), main domain of NSC (somatic, nutrition, psychosocial, functional, mobility, falls), living situation (independent, care at home), diagnostic tests, specialist seeing the patient and consulting specialists and ED-logistics (time of arrival at ED, duration of triage, triage colour).

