  - o Checking adherence to the recommended APOP-guidelines after completion

- 5. Tasks of the nurse:
  - Performing the APOP screening (potential)
  - Conventional care at the ED
  - Performing the ordered diagnostic tests
  - Performing actions following the APOP-risk score
- 6. Tasks of the doctor:
  - Conventional care at the ED
  - Ordering a standard set of diagnostics, at least: ECG, lab, urinalysis, X-thorax and bladder scan.
- 7. Actions following APOP-screening:
  - 1. Low risk, no supplementary actions recommended
  - 2. High risk of functional decline - the following actions are recommended among others; in case of suspected dehydration at presentation: starting early fluid administration, in case of admission: limiting the length of stay at the ED and organizing early transfer to the ward.
  - 3. High risk of cognitive decline - the following actions are recommended among others; Making sure the patient has a comfortable bed, has adequate lightning in the room and knows how to call for help.
  - 4. High risk of functional and cognitive decline - the following actions are recommended among others; consider the diagnosis delirium and an internist geriatric medicine or clinical geriatrician can be consulted for a comprehensive geriatric assessment after discharge from ED.
- 8. Discharge from the ED:
  - Possibilities include: admission to the ward, discharge to home, discharge to facility, discharge to short stay facility for primary care, discharge to geriatric rehabilitation.
  - Each study participant will be followed-up after leaving the care pathway.
  - A review of the medication list will be performed by the doctor at the ward, elderly care physician, the clinical pharmacologist or hospital pharmacist

- 9. Tasks of the research nurse / researcher:

- Collecting data for the database (see study parameters and endpoints)
- Collecting data for each participant 30 days after leaving the care pathway

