#### Endpoints are:

- Diagnostic procedures before and after implementation of the care path (quantity)
- ED length of stay – ED-LOS (in hours)
- Hospital length of stay – HOSP-LOS (in days)
- Readmissions in 90 days (yes/no)
- 30-day mortality
- Revisits in 30 days (yes/no)
- Patient satisfaction

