## **7. ADMINISTRATIVE ASPECTS, MONITORING AND PUBLICATION**

### **7.1 Handling and storage of data and documents**

All data will be handled confidentially. Participant data will be safeguarded and coded by a subject identification code, therefore he or she will not be identifiable. Data will be handled according to the Dutch Personal Data Protection Act and stored in Research Manager. When it is necessary to be able to trace data for an individual subject, a subject identification code list can be used to link the data. The key to this list will only be given to the principal investigator. Only qualified research personnel will have access to confidential data. Research data will be stored for at least 15 years.

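### Anonymous retrieval of controls does not fit a later nurse review of them, and printed follow-up differs between groups, so post-discharge comparisons are open to unequal ascertainment

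*Protocol*

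**What the plan says.** **Controls, CTcue hospitals.** Protocol section 5.1.4 has the control group obtained by a search of the electronic health record: "These data will be retrieved anonymously according to our defined in- and exclusion criteria, study parameters and endpoints". The same paragraph ends: "After 30 and 90 days, the research nurse will evaluate complications that occurred after the patient leaves the care pathway". The control paragraph of the summary (section 1) gives one time point only: "After 30 days, the research nurse will evaluate complications that occurred after the patient leaves the care pathway".

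**Controls, other hospitals.** Section 5.1.4 has the ED specialist keep the patient-number of eligible patients prospectively. The basis for doing without consent is, however, tied to anonymity: "The specialist in charge of the patient is allowed to use patient data for research, without consent when data is anonymised".

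**Pathway participants.** Section 5.3 item 8 promises follow-up after the pathway. Item 9 gives the research nurse or researcher the task of "Collecting data for each participant 30 days after leaving the care pathway".

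**Data handling.** Section 7.1 describes coded data for which "a subject identification code list can be used to link the data". It makes no exception for controls.

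**Endpoints.** The list in section 5.4.1 includes "30-day mortality", revisits within 30 days and readmissions within 90 days. Section 3 places mortality and readmissions or revisits among the secondary objectives.

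**The concern.** If a control record is truly anonymous when it leaves the hospital system, nobody can go back to that patient on day 30 or day 90. Either the data are coded, or the nurse review cannot be done as described. The protocol settles this neither way. Controls are gathered before implementation (section 5.1.5), and anonymisation cannot be undone at analysis, so the choice has to be made before control data are extracted.

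The second difficulty is that the two groups do not have the same follow-up on paper. The time points differ between sections, and the origin named for controls is an event they never have. Section 2 hopes for lower 30-day mortality and fewer readmissions. A before-and-after comparison of such events is only as good as the equality of the search for them. If one group is searched longer or more thoroughly, the difference in counts mixes the effect of the pathway with the effect of looking.

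**Working it through.** The plan gives no figure on this point to reproduce, so the check is mainly a comparison of the text.

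**Step 1. Follow-up as printed**

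| Item | Controls | Pathway participants |
|---|---|---|
| Identifiability | Anonymous retrieval (5.1.4, CTcue); patient-number kept, but use without consent tied to anonymised data (5.1.4, other hospitals) | Coded, with a list for re-linking (7.1) |
| Nurse or researcher time points | 30 and 90 days (5.1.4); 30 days only (summary) | 30 days only (5.3 item 9) |
| Origin | Leaving the pathway, which controls never enter | Leaving the pathway |
| Source of post-discharge events | CTcue query said to cover endpoints; nurse's source not named | Not named |

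**Step 2. What each endpoint needs**

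- Death and revisits at 30 days: both groups have a 30-day time point, but a different origin and no stated common source.
- Readmission at 90 days: section 5.1.4 gives controls a 90-day look. Section 5.3 item 9 stops at 30 days for pathway participants. Followed literally, readmissions from day 31 to day 90 would be sought in controls and not in the pathway group. If the summary applies instead, neither group has a stated 90-day look.
- ED length of stay: complete when the ED visit ends, so later follow-up cannot change it.

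**Step 3. Direction**

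- If nurse follow-up of pathway participants finds events outside the hospital record while controls yield only the record, controls are under-counted and the pathway looks worse.
- If the printed schedule is followed for readmissions, the pathway group is under-counted and the pathway looks better.
- If one hospital record serves both groups over the same window, this bias is absent.

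**Step 4. Illustration of size (assumed rates; the protocol gives none)**

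Inputs: 300 per group (section 5.1.5); no true effect; true event rate *p* of 5% to 20% (assumed); full capture in one group and a fraction *c* of 90% to 70% in the other (assumed).

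Spurious difference = *p*(1 − *c*); apparent risk ratio = 1/*c*. The chance of a two-sided p < 0.05 in that direction is Φ[(Δ − 1.96·SE₀)/SE₁], where Δ is the spurious difference, SE₀ = √[2p̄(1−p̄)/300] and SE₁ = √{[p₁(1−p₁)+p₂(1−p₂)]/300}.

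| True rate | Capture | Observed rates | Difference | Risk ratio | Chance of p < 0.05 |
|---|---|---|---|---|---|
| 5% | 90% | 5.0% vs 4.5% | 0.5 points | 1.11 | 4.7% |
| 10% | 80% | 10% vs 8% | 2 points | 1.25 | 13.5% |
| 20% | 70% | 20% vs 14% | 6 points | 1.43 | 49.9% |

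In the middle row, 2 points of 300 patients is 6 events (30 against 24). The sign depends on which group is searched less well. If only a fraction *f* of controls were affected (for example, those in CTcue hospitals), the difference would be *f*·*p*(1 − *c*); with *f* = 0.5 the middle row falls to 1 point. The protocol does not give *f*.

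**The case against.** A reader might infer that deaths and other events will be found from different sources in the two groups, so that controls are certain to be under-counted and the pathway made to look harmful. The documents do not support that.

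- No section names the source of post-discharge outcomes for either group. Item 9 of section 5.3 mentions no telephone call, general practitioner contact or registry. A research nurse is named for both groups, and the CTcue query is said to cover endpoints, so one hospital record could serve both.
- CTcue retrieval is retrospective. An extract run late enough would already hold the 30- and 90-day events in that hospital's record, with no need to return to anyone. The nurse sentence speaks of complications and does not name the listed endpoints.
- Anonymous retrieval is stated for CTcue hospitals only. Elsewhere the patient-number is kept, and the conflict is the weaker one with the anonymised-data condition. The protocol does not say how many controls fall under each route.
- For 90-day readmissions the literal schedule points the other way, to under-counting in the pathway group.
- The origin can be read sensibly: item 8 of section 5.3 treats leaving the pathway under discharge from the ED, so leaving the ED is probably meant for controls.

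All of this stands, and it limits the point to a risk of unknown size and direction. It does not remove the point. The late-extract reading makes the nurse review of controls redundant, yet the protocol orders that review. The likely origin is not written down for controls. The time points still disagree between the summary, section 5.1.4 and section 5.3.

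**Conclusion.** The point holds as a defect in how follow-up is fixed. In CTcue hospitals, anonymous retrieval and a later nurse review cannot both apply if the nurse must return to individual records, and anonymous retrieval does not fit section 7.1. Follow-up times differ between groups and between sections, and the control origin does not exist as worded.

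The comparisons of 30-day mortality, 30-day revisits and 90-day readmissions are therefore open to differential ascertainment. Under the assumed event rates and capture, the spurious difference is 0.5 to 6 percentage points in either direction. That range is illustration only; the protocol supplies nothing but the 300 per group. Actual unequal ascertainment is not established. ED length of stay, which drives the sample size, is untouched. The text should be corrected, but the point does not threaten that primary comparison.

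**What to change.** In section 5.1.4 and section 5.3 item 9, with the summary brought into line, state one rule for both groups:

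- Death, revisits and readmissions are read from the same hospital record fields.
- Look-up is at 30 days for death and revisits and at 90 days for readmissions.
- Days are counted from one origin that both groups have, the index ED visit.
- Events known only through direct contact with pathway participants are not used in these comparisons.

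Then choose one of two routes for identifiability:

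1. **Coded retrieval of controls**, with the key held at the hospital. First confirm that the hospitals' data-release form and the no-consent basis, which section 5.1.4 ties to anonymised data, allow it.
2. **Keep anonymity**, drop the nurse review of controls, and run the extract after the 90-day window has closed for both groups.

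The cost is a protocol amendment, with notification under section 7.2 if it is judged substantial, and for the first route the check on consent. Under either route, events outside the hospital are missed equally in both groups. Absolute rates will be low by an unknown amount, and the report should say so.
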